### Sample size

2.8

This study was developed according to the following hypotheses:

H_0_: *p*_1_ = *p*_2_H_1_: *p*_1_ ≠ *p*_2_

*p*_1_ = proportion of participants in the acupuncture group who achieved improvement, as measured by the predefined CEO after 6 weeks from baseline.

*p*_2_ = proportion of participants in the control group who achieved improvement, as measured by the predefined CEO after 6 weeks from baseline.

Based on our pilot study,^[15]^ the patients who achieved significant improvement was 44%, defined as a decrease in NRS, a reduction in PIS of BPI-SF scores of more than 20% from baseline, and change to “minimally improved”, “much improved”, or “very much improved” status, as measured by PGIC. Though there was no control group in the pilot study, we assumed that the conservative estimated proportion in the placebo group will be 10%.^[18]^ Assuming that the period and carryover effect does not exist, the difference in proportions of the 2 groups is 0.34 and within-subject SD is 0.34. Sixteen participants are required for each sequence group with a two-sided significance level of 5% (α = 0.05) and 90% power (1-β = 0.9). Consequently, a total of 40 patients (20 in each group) will be included, accounting for a potential 20% drop-out rate.

### Statistical analysis

2.9

The analysis set will consist of a modified intention-to-treatment (ITT) analysis set, a per protocol (PP) set, and a safety set. The modified ITT set will include the participants who were randomized, received acupuncture or conventional treatments, and have at least 1 effect assessment after treatment. The PP set will include only participants who received at least 1 assessment and completed the study protocol without major deviation. The safety set will include any participants who received at least 1 acupuncture or conventional treatment after randomization. The modified ITT analysis will be the main analysis of this study.

For the descriptive analysis, Student *t* test or a Wilcoxon rank sum test will be performed for continuous data, and a Chi-Squared test or Fisher exact test will be performed for categorical data.

For a confirmatory analysis, the primary endpoint is the proportion of participants who show improvement, as measured by the predefined CEO at 6 weeks after randomization. The carry-over effect will be checked with a linear mixed model, and if the carry-over effect is not significant, the improvement frequency and ratio at 6 weeks for each treatment period in each sequence group will be summarized. The difference of the overall improvement rate (δ) between the groups will be estimated, and the null hypothesis will be rejected as follows:$$\left|\frac{\overset{\circ }{\delta }}{{\overset{\circ }{\sigma }}_{d}/\sqrt{2n}}\right|>z_{0.05/2}$$

*σ*_*d*_: variance of the difference of the improvement rate between the groups within the subject

n: number of participants in each group

If the carry-over effect is significant, only data from treatment period A will be used and tested using the Chi-Squared test or Fisher exact test. Additionally, the carry-over effect, period effect, and sequence effect will be corrected using a generalized linear mixed model, and then the additional effects of acupuncture will be examined. At this time, the random effect, sequence, treatment period, and acupuncture treatment will be considered as fixed effects, and carry-over effect and period effect will be tested in terms of sequence order and treatment period, respectively. The term with a level of significance greater than 0.3 will be excluded from the model and the add-on effect of acupuncture treatment will be identified.

For secondary outcome measurements, continuous data will be summarized as mean, SD, median, and minimum/maximum value for each treatment period in each group, and compared between the 2 groups using a linear mixed model. Categorical data will be summarized as frequency and ratio for each treatment period in each group, and compared between the 2 groups using a generalized linear mixed model.

Statistical analyses will be performed by a statistician in the MRCC blinded to the group allocation using SAS Version 9.2 (SAS institute Inc., Cary, NC).

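### The primary test formula defines σ_d as a variance where a standard deviation belongs, the sample-size section mislabels 0.34 the other way round, and the normal cut-off is mildly liberal on 32 pairs

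*Protocol article*

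**What the plan says.** Protocol article, Statistical analysis (2.9): if carry-over is not significant, the overall difference in improvement rate δ is estimated and "the null hypothesis will be rejected as follows": the absolute value of δ-hat/(σ_d-hat/√(2n)) must exceed z(0.05/2). Here n is the number of participants per group. The symbol σ_d is defined as the "variance of the difference of the improvement rate between the groups within the subject". No small-sample correction is given.

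Protocol article, Sample size (2.8): 44% responders are taken from the pilot study for electroacupuncture. For control, "we assumed that the conservative estimated proportion in the placebo group will be 10" per cent. It continues: "the difference in proportions of the 2 groups is 0.34 and within-subject SD is 0.34". Then: "Sixteen participants are required for each sequence group with a two-sided significance level of 5" per cent and 90% power. Enrolment is 40, to allow for 20% drop-out.

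**The concern.** A mean difference divided by σ_d/√(2n) is a test statistic only if σ_d is a standard deviation. The protocol says variance. For a within-patient difference of two binary outcomes (−1, 0 or +1) the variance is usually well below 1, so it is smaller than the standard deviation. Using it in that place shrinks the standard error and inflates the statistic. This is the rule for the confirmatory primary analysis, so a programmer who follows the definition would run an invalid test.

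The Sample size section swaps the same two terms in the opposite direction, so it cannot be used to settle what σ_d means.

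A smaller question remains once σ_d is read correctly: whether a normal cut-off with an estimated spread holds 5% on about 32 pairs of binary responses.

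**Working it through.** **Inputs from the Sample size section.** p1 = 0.44, p2 = 0.10, δ = 0.34, two-sided α = 0.05, power 0.90, 16 per sequence (32 pairs), 40 enrolled. **Assumption, not in the protocol:** within-patient correlation of response, varied from 0 to 0.3. The null response rate is varied from 5% to 44%.

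**1. Reproduce the sample size.** n per sequence = (z_0.975 + z_0.90)² σ_d² / (2δ²), with (1.960 + 1.282)² = 10.507.
- Under independence the variance of the difference is 0.44×0.56 + 0.10×0.90 = 0.336, so the SD is about 0.58.
- With 0.34 as the variance: 10.507×0.34/(2×0.1156) = 15.45, so 16 per sequence. Power at 32 pairs is 91%. The protocol's figures reproduce.
- With 0.34 as the SD: 10.507×0.1156/(2×0.1156) = 5.25, so 6 per sequence.
- Drop-out: 32/0.80 = 40, as stated.

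So 0.34 is the variance, mislabelled.

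**2. The rejection rule with σ_d taken literally as a variance.** Rejecting when |δ-hat|/(σ²/√32) > 1.96 is the same as using a cut-off of 1.96×SD on the correct statistic. At a null rate of 10% with independence, the variance is 2×0.10×0.90 = 0.18 and the SD 0.424, so the effective cut-off is 0.83. At 44% the variance is 2×0.44×0.56 = 0.493 and the SD 0.702, so the effective cut-off is 1.38. Exact type I error comes from enumerating all counts of discordant pairs, with each discordant probability equal to p(1−p)(1−ρ).

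**3. The rule with σ_d as an SD.** The same enumeration was run with the overall sample SD, using z and then t on (pairs − 2) df.

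Type I error at 32 pairs:

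| Null rate | Correlation | σ_d as variance | SD with z | SD with t (30 df) |
|---|---|---|---|---|
| 10% | 0 | 37.2% | 6.7% | 4.8% |
| 10% | 0.3 | 43.6% | 5.0% | 4.3% |
| 20% | 0 | 25.5% | 7.0% | 4.3% |
| 27% | 0 | 21.1% | 6.6% | 4.4% |
| 27% | 0.3 | 28.6% | 7.2% | 4.3% |
| 44% | 0 | 16.8% | 6.3% | 4.9% |
| 44% | 0.3 | 23.9% | 6.9% | 4.3% |

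At a 5% null rate with independence, the z rule has about 3.3%. With the SD pooled within sequence, it has 5.7–6.3% under independence for rates of 10–44%. At 40 pairs with the overall SD, it has 4.9–6.2% over the same rates and correlations.

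**4. Power at 44% versus 10%, σ_d as an SD.**

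| Pairs | Correlation | z | t |
|---|---|---|---|
| 32 | 0 | 91.0% | 87.8% |
| 32 | 0.1 | 93.9% | 91.0% |
| 32 | 0.2 | 96.7% | 94.4% |
| 40 | 0 | 95.2% | 94.6% |

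At 32 pairs with zero correlation, the uncorrected and mid-p McNemar tests also have about 88%.

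**The case against.** The strongest reply is that a statistician would see at once that σ_d must be an SD, and that a normal cut-off matching a normal-theory sample size is an ordinary large-sample choice. The first part is fair as a forecast of what would probably happen. It does not make the written definition right, and the opposite slip in the sample-size section removes the obvious cross-check. On the second part, the excess over 5% is at most about 2 points, and it shrinks with 40 pairs or a low null rate.

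A reader might infer more: that the rule's true error is a fixed 6–7%, that 90% power is reached only through a liberal cut-off, and that the protocol should restate its power as 88%. The documents do not support this. The protocol fixes neither the within-patient correlation nor the variance estimator, and the z-rule error falls to 5.0% at its own 10% control rate with correlation 0.3. The 90% is correctly derived for the planned rule. A level-holding test drops to about 88% only at 32 pairs with zero correlation, and it exceeds 90% from a correlation of 0.1.

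It may also be said that the section names other analyses. The Chi-squared or Fisher test applies only if carry-over is significant, and the generalized linear mixed model is described as additional. Neither repairs the stated rule.

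**Conclusion.** The labelling errors are definite. The rule calls σ_d a variance where an SD is required, and the sample-size section calls a variance of 0.34 an SD. If the first were followed literally, type I error at 32 pairs would be about 17–44% for null rates of 10–44% and correlation 0–0.3. This does not show that the trial will be analysed that way, only that the text as written tells the analyst to.

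The normal cut-off is a lesser point. It gives about 5–7% at 32 pairs and 5–6% at 40 for null rates of 10–44%, and less than 5% if the null rate is about 5%. The sample size of 16 per sequence and the 90% power stand.

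All figures concern this rule alone, with complete pairs and no period effect. They do not include the carry-over test that precedes it, or any loss of pairs from the pain-score condition for entering the second treatment period.

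**What to change.** 1. In Statistical analysis, define σ_d as the standard deviation of the within-patient difference in response, and say whether it is estimated overall or pooled within sequence.
2. In Sample size, relabel 0.34 as the variance of that difference (SD about 0.58).
3. Replace z(0.05/2) with the t quantile on (number of pairs − 2) degrees of freedom, or use the uncorrected or mid-p McNemar test.
4. Optionally, beside the 90%, note that the t version has about 88% power at 32 pairs with zero correlation, above 90% with correlation of 0.1 or more, and about 95% if all 40 are evaluable.

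This changes a few lines of text and adds no patients. The price is about 3 points of power in the least favourable case shown (91.0% to 87.8% at 32 pairs under independence).

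### Section 2.9 defines σ_d in the primary test as a variance where the formula needs a standard deviation, and section 2.8 has the reverse mislabel

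*Protocol article*

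**What the plan says.** The protocol article, section 2.9 (Statistical analysis), sets out the primary analysis for the case where carry-over is not significant. The null hypothesis is rejected when |δ̂ / (σ̂_d/√(2n))| > z_0.05/2. Here δ is the difference in overall improvement rate and n is the number of participants per sequence group, so 2n is the total. The legend under the formula defines σ_d as the "variance of the difference of the improvement rate between the groups within the subject".

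Section 2.8 (Sample size) gives the planning values: "the difference in proportions of the 2 groups is 0.34 and within-subject SD is 0.34". It concludes that "Sixteen participants are required for each sequence group" at a "two-sided significance level of 5% (α = 0.05) and 90% power (1-β = 0.9"), and then adds an allowance for drop-out: "a total of 40 patients (20 in each group) will be included, accounting for a potential 20% drop-out rate".

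Nothing else in the article corrects either label.

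**The concern.** An estimate divided by (quantity/√N) is a z statistic only when the quantity is the standard deviation of a single observation, here one patient's difference in response between treatments A and C. A variance in that place gives the wrong standard error. When the variance is below 1, as it is for this 0/1 outcome at the rates considered here, it is smaller than its own square root. The standard error would then be too small and the statistic too large by a factor of 1/SD.

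This matters because the line belongs to the prespecified decision rule of the confirmatory analysis. An analyst who follows the legend rejects too often. One who follows the usual formula departs from the written definition without a recorded reason. Section 2.8 does not settle the question, because its label is reversed too: the number it calls an SD behaves as a variance.

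**Working it through.** **Inputs.** From section 2.8: responder rates 0.44 (pilot) and 0.10 (assumed control), δ = 0.34, two-sided α = 0.05, power 90%, 16 per sequence, 20% drop-out. From section 2.9: the rejection rule and the definitions of σ_d and n. The responder rate under the null hypothesis and the within-subject correlation ρ are not given. They are assumptions below.

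**Step 1: reproduce the sample size.** For a two-period cross-over analysed on within-subject differences with variance V,

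n per sequence = (z_0.975 + z_0.90)² × V / (2δ²) = (1.960 + 1.2816)² × V / (2 × 0.34²).

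| Reading of 0.34 | V | n per sequence |
|---|---|---|
| Variance of the difference | 0.34 | 15.45, so 16 |
| SD of the difference, close to the label | 0.34² = 0.1156 | 5.25, so 6 |
| SD of a single measurement | 2 × 0.34² = 0.2312 | 10.51, so 11 |

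Only the first reading gives the stated 16. The planning rates lead to the same value: with independent responses, V = 0.44×0.56 + 0.10×0.90 = 0.2464 + 0.0900 = 0.3364. This rounds to 0.34 and again gives 16 (15.29). The corresponding SD is √0.3364 = 0.58. The drop-out step also reproduces: 32/(1 − 0.20) = 40.

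**Step 2: type I error if the section 2.9 legend is applied literally.** With V in place of √V, the rule rejects when the correct z statistic exceeds 1.96 × √V in absolute value. The two-sided error is therefore 2[1 − Φ(1.96√V)]. Under the null hypothesis with common rate p, V = 2p(1 − p)(1 − ρ). At ρ = 0:

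| p | V | 1.96√V | Two-sided error |
|---|---|---|---|
| 0.10 | 0.18 | 0.83 | 40.6% |
| 0.25 | 0.375 | 1.20 | 23.0% |
| 0.40 | 0.48 | 1.36 | 17.4% |
| 0.50 | 0.50 | 1.39 | 16.6% |

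At V = 0.34, the protocol's own figure read as a variance, the error is 25.3%, and the statistic is inflated by 1/0.58 = 1.72.

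**Step 3: sensitivity to correlation.** Positive ρ lowers V and raises the error. At ρ = 0.3 it is 25% (p = 0.44) to 49% (p = 0.10). At ρ = 0.5 it is 33% to 56% over the same rates.

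**Step 4: simulation with estimated variances, ρ = 0, p from 0.10 to 0.44, 400,000 trials per setting.**
- Literal rule, one overall variance: 17% to 37% with 16 per sequence, 18% to 47% with 20.
- Literal rule, pooled within-sequence variance, at p = 0.10 and 0.44: 18% to 41% with 16, 18% to 47% with 20.
- Square root taken, as the formula needs: 6.4% to 6.7% with 16 and 5.3% to 5.7% with 20 (overall variance); 5.6% to 6.1% and 5.6% to 5.7% respectively (pooled).

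**Step 5: power with the correct reading.** With SD = √0.34 = 0.583, power = Φ(0.34 × √(2n)/0.583 − 1.96). This is 91% at 16 per sequence and 96% at 20.

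**The case against.** The strongest reply is that this is a wording error in a symbol legend. The symbol σ, the division by √(2n) and the comparison with a normal quantile all point to a standard deviation, and an experienced trial statistician would very probably take the square root. The sample size supports this reading: the designers put the variance in the right place and gave it the wrong name. A superscript in the legend may also have been lost, so that the source defines σ_d² as the variance. Finally, section 2.9 plans an additional generalized linear mixed model that does not use σ_d and would show up an implausible z value.

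Much of this stands. A reader might infer from the error rates that the trial will run at a 17% to 41% false-positive rate. The protocol does not support that: the inflation arises only under literal application. Nor is 17% to 41% a property of the design, since it rests on null rates and a zero correlation that the protocol does not state. A reader might also infer that the sample size is wrong. It is not; 16 per sequence and 40 in total reproduce once 0.34 is read as a variance. The section 2.8 label has no effect on the type I error of the test.

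What does not stand is that the definition can be left alone. The word variance is in the text, a lost superscript cannot be shown, and it would not explain the label in section 2.8. The mixed model is additional to the stated rule and does not replace it.

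**Conclusion.** The definition of σ_d in section 2.9 is wrong for the place where it is used, and the label on 0.34 in section 2.8 is wrong in the opposite direction. An SD was probably intended in the test, so the likely fault is mislabelling, not a miscalculation. It still needs correcting because it sits in the confirmatory decision rule, which should be executable as written.

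If taken literally, the rule has a two-sided type I error of about 17% (null rate 50%) to 41% (null rate 10%) at zero within-subject correlation, by normal approximation. The upper figure is not a ceiling: positive correlation raises it, and so does the discreteness of the outcome at low rates (47% simulated at a rate of 10% with 20 per sequence). For null rates across this range and non-negative correlation, the approximation does not fall below 16.6%, more than three times the nominal 5%.

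**What to change.** In section 2.9, define σ_d as the standard deviation of the within-subject difference in composite response (A minus C), estimated as the square root of the pooled within-sequence sample variance of those differences. Leave the rest of the formula as it is.

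In section 2.8, relabel 0.34 as the variance of that within-subject difference (SD about 0.58). Correct both places together, in the full protocol and in any analysis plan that repeats them, before the data are analysed.

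The cost is a few words in two places. The sample size, visits and data collection do not change.

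### The only period-adjusted analysis of the primary endpoint breaks down when control responders are few, and the p > 0.3 exclusion rule rescues it only by dropping adjustment terms

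*Protocol article*

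**What the plan says.** Section 2.9 (Statistical analysis) makes the confirmatory test a z-test on the overall difference in improvement rate, with no period term. If carry-over is significant, a chi-squared or Fisher test on part of the data replaces it. The section then adds a further model: "Additionally, the carry-over effect, period effect, and sequence effect will be corrected using a generalized linear mixed model". Its fixed effects are sequence, treatment period and acupuncture, followed by a selection rule: "The term with a level of significance greater than 0.3 will be excluded from the model". The acupuncture effect is read from what remains. The link function, the type of test and the fitting method are not stated.

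Section 2.8 (Sample size) gives the planning figures. For acupuncture, "the patients who achieved significant improvement was 44" per cent; for control, "we assumed that the conservative estimated proportion in the placebo group will be 10" per cent. It continues: "Assuming that the period and carryover effect does not exist", "the difference in proportions of the 2 groups is 0.34 and within-subject SD is 0.34". The result is "Sixteen participants are required for each sequence group with a two-sided significance level of 5% (α = 0.05) and 90% power", raised to 20 per sequence for 20% drop-out.

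**The concern.** A cross-over result is normally expected to hold after adjustment for period. Here one model carries that adjustment for the primary treatment effect, so it should work at the numbers the trial was planned on.

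Two features make that doubtful. First, three fixed effects plus an intercept use up all four sequence-by-period cells, and each control cell expects only 16 × 0.10 = 1.6 responders. One empty control cell sends the treatment log odds ratio to infinity. Second, the exclusion rule can bring the estimate back only by removing sequence or period, which are the adjustments the model was added to provide. A clear risk difference could then stand beside an adjusted analysis that either shows nothing or no longer adjusts.

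**Working it through.** **Inputs (2.8):** p1 = 0.44, p2 = 0.10, 16 evaluable per sequence, 20 enrolled per sequence, two-sided 5%, 90% power, no period or carry-over effect. **Assumed, because not stated:** logit link, Wald test, within-patient correlation.

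**1. The plan's own figure.** Under independence the variance of the within-patient difference is 0.44 × 0.56 + 0.10 × 0.90 = 0.3364. Then n per sequence = (1.960 + 1.282)² × 0.3364 / (2 × 0.34²) = 15.3, so 16, and 32 / 0.8 = 40 in total. Power of the z-test at 16 is Φ(0.34 / √(0.3364/32) − 1.96) = Φ(1.36) ≈ 91%. The figure reproduces if the second 0.34 in 2.8 is read as this variance. The trial is therefore sized on the risk-difference scale.

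**2. Empty cells in the full model.** Leaving the random effect aside, the fitted treatment log odds ratio is half of [logit(AC, period 1) − logit(AC, period 2) − logit(CA, period 1) + logit(CA, period 2)]. It is infinite if either control cell has no responders.
- 16 per sequence: 0.9^16 = 0.185 per cell; 1 − (1 − 0.185)² = 33.6%.
- 20 per sequence: 0.9^20 = 0.122 per cell; 1 − (1 − 0.122)² = 22.8%.
- Other control rates at 16 per sequence (assumed range): 69% at 5%, 14% at 15%, 6% at 20%.

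Within-patient correlation does not alter these figures, because the two control cells hold different patients.

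**3. After the exclusion rule.** With an empty cell, the Wald p-values of sequence and period are near 1, so a term goes. Three parameters then describe four cells, the three non-empty cells determine them, and the estimate is infinite only if both control cells are empty: 0.9^32 = 3.4% at 16 per sequence, 0.9^40 = 1.5% at 20.

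**4. Simulated power** (44% vs 10%, no period effect, zero correlation, 16 per sequence; 400 to 20,000 trials by method):

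| Analysis | Power |
|---|---|
| Full model, Wald | 51-55% |
| After exclusion, Wald: quadrature | 72-73% |
| After exclusion, Wald: pseudo-likelihood | 81% |
| After exclusion, Wald: plain logistic | 86% |
| Full model, likelihood-ratio | about 91% |
| Period-adjusted risk difference, t-test | 89% |
| Exact Mainland-Gart test | 77% |
| Plan's z-test | about 91% |

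At 20 per sequence, Wald power is 67-73% for the full model and 89-93% after exclusion, against 96% by formula for the z-test. With an assumed latent correlation of 0.4 at 16 per sequence, power after exclusion is 56% by quadrature and 88% by pseudo-likelihood, against 96% for the z-test. In trials with an empty cell the full-model Wald test never rejected; the risk difference rejected in about 98% of them.

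**5. What exclusion removes.** With no true period effect, period was dropped in 74% of simulated trials. That is close to what the rule implies: a valid p-value for an absent effect exceeds 0.3 in 70% of trials. A real period effect would be dropped less often.

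**6. The alternative.** Let π be the period shift. The mean A-minus-C difference is δ − π in sequence AC and δ + π in CA; their simple average is δ at any sequence sizes, and it exists with empty control cells. Simulated type I error (assumed correlation 0.2) was 4.2% at 10% vs 10% and 5.0% at 27% vs 27%.

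**The case against.** The strongest reply is that the plan does not stop at the full model. The reported effect comes after exclusion, where a non-finite estimate is rare. This stands: a reader might infer that a third of trials would yield no adjusted estimate, and the document does not support that.

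Next, link, test and fitting method are details an article may leave to a statistical analysis plan, and a likelihood-ratio test would remove most of the power loss. This also stands, so the power figures are conditional. The terms and the exclusion rule, however, are fixed in 2.9 whatever those details turn out to be.

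Third, the model is supplementary. A reader might infer that the primary result is underpowered; it is not, since the z-test keeps about 91%. With equal sequences a period shift also cancels from the pooled difference. With unequal sequences it does not: at an assumed 16 AC and 12 CA patients the pooled estimate moves by π × (12 − 16)/28 = −π/7, or about −0.014 for an assumed shift of 0.10. Imbalance is plausible, because under 2.2.2 a patient averaging below 4 after washout stays on treatment C. As I read it, this removes acupuncture data only from sequence CA.

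Two further inferences are not supported. Terms are not dropped because a cell is empty: period was dropped about as often without an empty cell (74%) as with one (72%). Nor does the point extend to the secondary outcomes, where no binary outcome with a low control rate is identified.

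**Conclusion.** The point holds for the supplementary analysis only. As specified, it offers either a full model that is often not estimable at the planning figures, or a data-selected model that usually no longer adjusts for period. The non-finite figures rest on the 10% control rate and a logit link, and fall quickly as the control rate rises. The power figures rest also on Wald testing and zero correlation, and the spread after exclusion shows how far the result would depend on the fitting method. The frequency with which period is dropped assumes no true period effect. The confirmatory test needs no change on this account. The change is worth making because a stable period-adjusted analysis exists on the scale the trial was sized on.

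**What to change.** In 2.9, for the composite responder endpoint:

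- Make the supplementary period-adjusted analysis the mean of the two sequence-specific mean within-patient A-minus-C differences, reported as a risk difference with a t-based 95% confidence interval on 2n − 2 degrees of freedom (n per sequence; 30 at 16 per sequence).
- Remove the p > 0.3 exclusion rule.
- Optionally, add an exact sequence-stratified test on discordant patients (Mainland-Gart) as a sensitivity analysis.
- If an odds ratio is also wanted, keep all three terms and use a penalised-likelihood fit or a likelihood-ratio test, not a Wald test.

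The cost is a few sentences and simple code, with no extra data or patients. The downsides are small: the adjusted effect is a risk difference rather than an odds ratio, and the exact test is conservative.
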